### 17.3 Analysis of Efficacy Parameters

The analyzes for primary end-points will be carried out when the last study subject has reached the milestone of analyzes and all the CRF collected information related to end-point is available.

The analyzes for secondary and explotory outcomes will be carried out after the last subject has reached the second screening round visit and/or end-of-study (3y), which ever is feasible, and all the CRF collected information related to end-point is available.

### 17.4 Planned Interim Analysis

There is no predefined interim analysis. Interim analyses on efficacy, and selected biomarkers may be provided on ongoing basis prior to completion of the trial in order to expedite conclusions and to support trial presentations or publications.

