#### 14.2 Device Data

Data will be collected within a cloud-based platform(s), for processing, analysis and storage, managed by the sponsor. Only identified and trained users access this system. Device data may be analyzed on an ongoing basis for the purpose of device changes.

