## 16. END OF TRIAL DEFINITION

The end of trial will be the date the overall survival and lung cancer data of the last subject has been collected. The Sponsor will notify relevant regulatory authorities and ethics committees that the trial has ended at the appropriate time and will provide them with a summary of the clinical trial report within 12 months of the end of trial.

The Sponsor reserves the right to stop the trial at any time on the basis of new information regarding safety or efficacy (e.g., discovery of an unexpected, significant or unacceptable risk to the subjects enrolled in the trial), or if trial progress is unsatisfactory (e.g., failure to enroll subjects at an acceptable rate), or for other valid reasons (e.g., Sponsor decides to suspend or discontinue development of the drug). After such a decision is made, the Investigator must inform all on-trial subjects within one (1) week. All delivered trial materials must be collected and all e-CRF pages completed to the extent possible.

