### 17.2 Analysis of Outcome Measures

#### 17.2.1 Primary Outcomes

- The percentage of subjects who are actively smoking at 3 months after inclusion between the study arms
- The percentage of subjects who are actively smoking at 6 months after inclusion between the study arms

Eligible subjects are randomized (1:1) with stratification according to pack years (<30py or ≥30py), and age (<65 or ≥65v) to smartphone based smoking cessation and control arm.

The study is powered (80%) with 155 subjects to detect 15% difference in (75 vs. 90%) in the number of active smokers at three and six months after inclusion with 90% confidence. With the expected dropout rate, the sample size is adjusted to 200.

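### Section 17.4 leaves efficacy looks before completion open-ended, with no boundary or access rule, although the 10% level is spent in full at one final test

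*Protocol*

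**What the plan says.** Section 17.4 opens by stating that no interim analysis is predefined. Its next sentence reads: "Interim analyses on efficacy, and selected biomarkers may be provided on ongoing basis prior to completion of the trial", so as to speed up conclusions and support presentations or publications. It gives no number or timing of looks, no adjusted significance level, and no rule on who may see the results.

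Three other places bear on this:

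- **Section 17.3**, on efficacy parameters: "The analyzes for primary end-points will be carried out when the last study subject has reached the milestone of analyzes", with the related CRF data available. The primary end-points are therefore treated as efficacy, and their analysis has a fixed time.
- **Section 16**: "The Sponsor reserves the right to stop the trial at any time on the basis of new information regarding safety or efficacy". No boundary is attached to the efficacy ground. The same section defines the end of trial as collection of the last subject's survival and lung cancer data. Section 1 limits that follow-up to 3 years from inclusion.
- **Section 17.2.1**: the target is a difference of 75% against 90% "in the number of active smokers at three and six months after inclusion with 90% confidence", with 80% power and 155 subjects. "With the expected dropout rate, the sample size is adjusted to 200".

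Smoking status at 3 and 6 months is taken by telephone (section 7.2.1). It can be checked against app data in the experimental arm only. One arm receives the app plus written material and the other written material alone (section 7.2). No blinding is described.

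**The concern.** Sections 17.3 and 17.4 disagree on when the primary smoking results may be examined. Section 17.3 fixes one time. Section 17.4 permits efficacy analyses at any time before completion and names conclusions as a purpose, and section 16 adds an unbounded right to stop on efficacy. The sample size leaves nothing in reserve for earlier tests.

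Two things are at stake. The first is the false-positive rate: several tests at the same nominal level, any of which may support a claim or a stop, together exceed that level. The second is the outcome itself. It is a self-report over the telephone in arms that subjects can tell apart. If staff or participants learn that one arm is ahead while calls are still being made, later answers may shift.

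This is not detail left to a statistical analysis plan. The protocol itself grants the permission.

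**Working it through.** **Inputs from the protocol.** Active smokers 75% against 90%; power 80%; 90% confidence; 155 evaluable, raised to 200; allocation 1:1 (section 17.2.1). Enrolment about 6 months (section 1, Trial Duration). Calls at 3 and 6 months, with a window of one month in Table 1 and two weeks in section 7.2.1. Sidedness is not stated. Two-sided 10% has the same critical value, 1.645, as one-sided 5%.

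**Step 1. Reproduce the sample size.**

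- Unpooled variance: n per arm = (1.645 + 0.842)² × (0.75×0.25 + 0.90×0.10) / 0.15² = 76.25, so 77 per arm and 154 in total.
- Pooled variance under the null: 79 per arm, 158 in total.
- Power with 77.5 per arm is 79.6%.
- Two-sided 5% needs 194 to 200, and one-sided 10% needs 112 to 114. Neither matches.

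The stated 155 is therefore sound for one test that uses the whole two-sided 10%. The rise to 200 implies a dropout of 1 − 155/200 = 22.5%. It is an allowance for losses, not for extra looks.

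**Step 2. Error over repeated looks.** Assume K equally spaced looks, with Z_k = (X_1 + … + X_k)/√k and independent standard normal increments. The null is rejected if any |Z_k| exceeds 1.645. K is an assumption because the protocol gives none. Results from 1,000,000 simulated trials:

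| Looks | Two-sided error | Direction of benefit only |
|---|---|---|
| 1 | 9.9% | 5% (nominal) |
| 2 | 16.1% | 8.1% |
| 3 | 20.2% | 10.1% |
| 5 | 26.0% | 13.0% |

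A binomial check with up to 100 per arm, and the same proportion of active smokers in both arms (90% or 82.5%), gives 15.8–16.5% for 2 looks, 21.3–21.8% for 3 and 26.2–27.2% for 5. A single test gives 9.9–10.2%.

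**Step 3. What would hold 10% if looks were kept.** Pocock-type levels per look are 0.061 (2 looks), 0.046 (3) and 0.034 (5). An O'Brien–Fleming type with 2 looks uses 0.018, then 0.093.

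**Step 4. Calendar.** The first 3-month outcomes arrive at about month 3, while enrolment is still open. The last 6-month call falls at 6 + 6 = 12 months after first enrolment, or 13 with the one-month window. The last subject's 3-year follow-up ends at about 6 + 36 = 42 months. The period in which by-arm results could do harm is thus roughly months 3 to 13. From the lock onward the full primary result can be reported without any interim look.

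If the milestone in section 17.3 is read separately for each end-point, the 3-month analysis could be run at about 6 + 3 = 9 months. With uniform accrual (an assumption), the second half of subjects enrolled would still await their 6-month call.

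**The case against.** The strongest reply is that section 17.4 is harmless when read with sections 16 and 17.3. Completion of the trial lies years after the primary outcome, and section 17.3 already fixes the primary analysis. On that reading section 17.4 merely allows the finished smoking result and the biomarkers to be reported before long-term follow-up ends, which inflates nothing. That use is legitimate and should be kept. But section 17.4 does not confine itself to data past the milestone, so the reading is possible rather than stated.

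It can also be said that section 16 is a general reservation whose example is an unacceptable risk, and that new efficacy information may include outside evidence or lack of effect. This is fair, and it argues against deleting the clause. It does not supply a boundary for stopping on the trial's own by-arm results.

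A reader might infer more than the documents support:

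- *That section 17.4 denies any interim analysis and then allows one.* It says only that none is predefined, so the two sentences do not contradict each other.
- *That the 10% level is already lost.* The loss is conditional on looks being made and being able to support a conclusion or a stop. Ten looks would give 34%, but nothing in the protocol suggests that many.
- *That the 3-month analysis under section 17.3 is a repeated look.* Once all 3-month data are in, it is the full analysis of that end-point. Having two primary time points is a separate multiplicity question and is not in these figures.
- *That section 14.2 spends alpha.* It says "Device data may be analyzed on an ongoing basis for the purpose of device changes", which involves no between-arm test. Whether the app changes during the trial is a separate matter.
- *That the trial is declared open-label with unblinded callers.* The protocol uses no such term. Visible arms and the absence of described blinding are all that can be said.

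**Conclusion.** The point holds in its conditional form. The protocol permits efficacy looks without limit of number, boundary or access, and stopping on efficacy without a boundary. This conflicts with its own fixed time for the primary analysis and with a sample size that uses the full level once. The sample size of 155 is not in error.

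The size of the inflation in Step 2 rests on three assumptions: equally spaced looks, each tested at two-sided 10%, and any of them able to support a conclusion or a stop. Sections 17.4 and 16 allow the last; the first two are not fixed by the protocol. The influence of interim results on later self-reports is plausible from the design but cannot be quantified from the document.

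**What to change.** Replace the second sentence of section 17.4 with wording such as:

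> *No analysis of smoking outcomes by arm is done, shown or published until the 6-month status of the last randomised subject has been recorded and the primary data are locked. The 3- and 6-month end-points are analysed together at that point. Results may then be reported before the end of the 3-year follow-up. Until then, only pooled summaries of recruitment, LDCT, biomarkers and safety may be reported.*

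Add to section 16 that the trial's own by-arm smoking results are not a basis for stopping for benefit before that lock. The reservations on safety, outside information and poor enrolment stay as they are. Align section 17.3 so that the milestone for both primary end-points is the same lock.

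This keeps the error for one comparison at 10% (simulated 9.9%) without extra subjects or visits. If the sponsor does want interim looks, section 17.4 should state their number, timing, boundary and who has access, using levels such as those in Step 3.

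The cost is a protocol amendment and a delay: by-arm conference results wait until the lock, about 12 to 13 months after first enrolment if enrolment takes the estimated 6 months, plus the time to lock the data. For section 14.2, at most log the app version used by each subject; error control asks for nothing more there.

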## 18. ACCESS TO SOURCE DATA AND RELATED DOCUMENTS

By participating into this trial, the Investigator(s) and the site(s) conducting this trial will permit trial-related monitoring, audits, Institutional Review Board or equivalent review, and regulatory inspection(s) and provide direct access to source data/documents. A reasonable time must be given for the site(s) to prepare for such activities.

## 19. TRIAL ORGANIZATIONAL STRUCTURE

### 19.1 Sponsor

The Sponsor of the trial is Oulu University Hospital. The Sponsor may delegate duties to trial sites.

### 19.2 Finance

The Sponsor will make contracts with trial sites.

## 20. ETHICAL CONSIDERATION

The trial will be performed in accordance with the recommendations guiding physicians in biomedical research involving human subjects, adopted by the 18th World Medical Association General Assembly, Helsinki, Finland, June 1964, amended at the 64th World Medical Association General Assembly, Fortaleza, Brazil, October 2013 (website: <https://www.wma.net/policies-post/wma-declaration-of-helsinki-ethical-principles-formedical-research-involving-human-subjects/>).

The trial will be conducted in accordance with the European Union directive 2001/20/EC, data protection regulation (Regulation (EU) 2016/679) local laws, and the ICH GCP E6(R2). This trial will be carried out under a Clinical Trial Authorization in accordance with local regulations. The protocol will be submitted to and approved by the corresponding ethical committees.

Before any subjects are enrolled into the trial, the Principal Investigator at each site is required to obtain corresponding approval. Sites will not be permitted to enroll subjects until written confirmation of approval is received.

It is the responsibility of the Principal Investigator to ensure that all subsequent amendments gain the necessary local approval. This does not affect the individual clinicians' responsibility to take immediate action if thought necessary to protect the health and interest of individual subjects.

## 21. CONFIDENTIALITY AND DATA PROTECTION

All trial findings and documents will be regarded as confidential. The Investigator and members of their research team must not disclose any information without prior written approval from the Sponsor. The Investigator must maintain documents not for submission to the Sponsor in strict confidence. In the case of specific issues and/or queries from the regulatory authorities, it will be necessary to have access to the complete trial records, provided that subject confidentiality is protected.

Subjects will be identified on the CRF and other documents submitted to the Sponsor or Sponsor's representative by their trial subject number. Documents that identify the subject must not be submitted to the Sponsor and must be maintained in confidence by the Investigator. Only the Investigator and authorized staff will be able to enter and correct data in the CRF.

CRF documents should be completed for each subject included in the trial and should reflect the latest observations on the subjects participating in the trial. Therefore, the CRF is to be completed as soon as possible during or immediately after the subject's visit or assessment. The Investigator must verify that all data entries in the CRF are accurate and correct. If some assessments cannot be done, or if certain information is unavailable, not applicable or unknown, the Investigator should indicate this in the CRF.

All discrepancies must be resolved online directly by the Investigator or by staff authorized to do this by Delegation of Authority. The Investigator will be required to sign off the clinical data recorded in the CRF.

## 22. PUBLICATION POLICY

Any manuscript, abstract or other publication or presentation of results or information arising in connection with the trial (including any ancillary trial involving trial subjects) must be prepared in conjunction with the trial Sponsor. The Sponsor will review the communications for accuracy to avoid potential discrepancies with submissions to health authorities, verify that confidential information is not accidentally disclosed, and provide any relevant supplementary information. The Sponsor's comments on the proposed publication shall be considered in good faith by the authors. The Sponsor may delay such submission by a maximum of 90 days if it reasonably believes that publication of results may compromise its intellectual property rights or may insist that such information or data is removed from the proposed publication. Publication of the results will not include confidential information without the permission of the Sponsor.

The original CRF pages and all data generated during the trial under this protocol will become the property of the Sponsor.

The Sponsor may announce quality-assured summary data in order to comply with the requirements of financial regulatory authorities, while ensuring so far as possible that such announcements will not compromise the Investigators' ability to publish the data in appropriate scientific forums. Authorship of

communications arising from the trial-related data and subsequent analysis may include members from the contributing site(s) including basic research laboratories and Sponsor's personnel.

## APPENDIX 1 - WMA DECLARATION OF HELSINKI

Adopted by the 18th WMA General Assembly, Helsinki, Finland, June 1964 and amended by the:  
29th WMA General Assembly, Tokyo, Japan, October 1975  
35th WMA General Assembly, Venice, Italy, October 1983  
41st WMA General Assembly, Hong Kong, September 1989  
48th WMA General Assembly, Somerset West, Republic of South Africa, October 1996  
52nd WMA General Assembly, Edinburgh, Scotland, October 2000  
53rd WMA General Assembly, Washington DC, USA, October 2002 (Note of Clarification added)  
55th WMA General Assembly, Tokyo, Japan, October 2004 (Note of Clarification added)  
59th WMA General Assembly, Seoul, Republic of Korea, October 2008  
64th WMA General Assembly, Fortaleza, Brazil, October 2013

### Preamble

1. The World Medical Association (WMA) has developed the Declaration of Helsinki as a statement of ethical principles for medical research involving human subjects, including research on identifiable human material and data. The Declaration is intended to be read as a whole and each of its constituent paragraphs should be applied with consideration of all other relevant paragraphs.
2. Consistent with the mandate of the WMA, the Declaration is addressed primarily to physicians. The WMA encourages others who are involved in medical research involving human subjects to adopt these principles.

### General Principles

3. The Declaration of Geneva of the WMA binds the physician with the words, "The health of my patient will be my first consideration," and the International Code of Medical Ethics declares that, "A physician shall act in the patient's best interest when providing medical care."
4. It is the duty of the physician to promote and safeguard the health, well-being and rights of patients, including those who are involved in medical research. The physician's knowledge and conscience are dedicated to the fulfilment of this duty.
5. Medical progress is based on research that ultimately must include studies involving human subjects.
6. The primary purpose of medical research involving human subjects is to understand the causes, development and effects of diseases, and improve preventive, diagnostic and therapeutic interventions (methods, procedures and treatments). Even the best proven interventions must be evaluated continually through research for their safety, effectiveness, efficiency, accessibility and quality.
7. Medical research is subject to ethical standards that promote and ensure respect for all human subjects and protect their health and rights.
8. While the primary purpose of medical research is to generate new knowledge, this goal can never take precedence over the rights and interests of individual research subjects.
9. It is the duty of physicians who are involved in medical research to protect the life, health, dignity, integrity right to self-determination, privacy, and confidentiality of personal information of research subjects. The responsibility for the protection of research subjects must always rest with the physician or other health care professionals and never with the research subjects, even though they have given consent.
10. Physicians must consider the ethical, legal and regulatory norms and standards for research involving human subjects in their own countries as well as applicable international norms and standards. No national or international ethical, legal or regulatory requirement should reduce or eliminate any of the protections for research subjects set forth in this Declaration.

11. Medical research should be conducted in a manner that minimizes possible harm to the environment.
12. Medical research involving human subjects must be conducted only by individuals with the appropriate ethics and scientific education, training and qualifications. Research on patients or healthy volunteers requires the supervision of a competent and appropriately qualified physician or other health care professional.
13. Groups that are underrepresented in medical research should be provided appropriate access to participation in research.
14. Physicians who combine medical research with medical care should involve their patients in research only to the extent that this is justified by its potential preventive, diagnostic or therapeutic value and if the physician has good reason to believe that participation in the research study will not adversely affect the health of the patients who serve as research subjects.
15. Appropriate compensation and treatment for subjects who are harmed as a result of participating in research must be ensured.

### **Risks, Burdens and Benefits**

16. In medical practice and in medical research, most interventions involve risks and burdens. Medical research involving human subjects may only be conducted if the importance of the objective outweighs the risks and burdens to the research subjects.
17. All medical research involving human subjects must be preceded by careful assessment of predictable risks and burdens to the individuals and groups involved in the research in comparison with foreseeable benefits to them and to other individuals or groups affected by the condition under investigation. Measures to minimize the risks must be implemented. The risks must be continuously monitored, assessed and documented by the researcher.
18. Physicians may not be involved in a research study involving human subjects unless they are confident that the risks have been adequately assessed and can be satisfactorily managed. When the risks are found to outweigh the potential benefits or when there is conclusive proof of definitive outcomes, physicians must assess whether to continue, modify or immediately stop the study.

### **Vulnerable Groups and Individuals**

19. Some groups and individuals are particularly vulnerable and may have an increased likelihood of being wronged or of incurring additional harm. All vulnerable groups and individuals should receive specifically considered protection.
20. Medical research with a vulnerable group is only justified if the research is responsive to the health needs or priorities of this group and the research cannot be carried out in a non-vulnerable group. In addition, this group should stand to benefit from the knowledge, practices or interventions that result from the research.

### **Scientific Requirements and Research Protocols**

21. Medical research involving human subjects must conform to generally accepted scientific principles, be based on a thorough knowledge of the scientific literature, other relevant sources of information, and adequate laboratory and, as appropriate, animal experimentation. The welfare of animals used for research must be respected.
22. The design and performance of each research study involving human subjects must be clearly described and justified in a research protocol. The protocol should contain a statement of the ethical considerations involved and should indicate how the principles in this Declaration have been addressed. The protocol should include information regarding funding, sponsors, institutional affiliations, potential

conflicts of interest, incentives for subjects and information regarding provisions for treating and/or compensating subjects who are harmed as a consequence of participation in the research study. In clinical trials, the protocol must also describe appropriate arrangements for post-trial provisions.

